#### Process evaluation

Next to an effect evaluation, the process of the intervention will be evaluated in three ways. First, at post-test the participants in the intervention group will be asked for their opinions about 1) the intervention as a whole; 2) the counsellors' competence; 3) the visits to the OHS, the telephone calls and the written materials; and 4) the effect of the intervention on their own behaviour change. Second, by asking a random sample of the counsellors to tape-record two of their conversations, the quality of MI will be assessed, as described before. Third, by means of forms filled in by the counsellor after each conversation, the amount and duration of each conversation will be assessed, the main subject of each conversation, whether long-term goals have been achieved, et cetera.

### Data analysis

On all outcome measures, intention-to-treat analyses will be performed. Both crude and adjusted linear and logistic regression analyses will be performed. In doing so, analysis for covariance will be conducted adjusting for the outcome variable measured at baseline. In the adjusted model, other potential confounders will be included as covariate, such as age and work activities. Furthermore, effect modification, e.g. by family history, will be checked. First of all, data will be analysed for the whole intervention group, that is, irrespective of the intervention received. Secondly, subgroup analysis will be done among those having received the smoking or the energy balance intervention. As all participants will have to indicate at baseline which lifestyle behaviour they prefer to change, the participants in each intervention subgroup will be compared to those in the control group having indicated the same type of intervention preference. Cost-effectiveness ratios will be calculated by dividing the difference between the mean total costs between the two study groups by the difference in the mean effects. For each outcome measure used in this evaluation, cost-effectiveness ratios will be presented graphically on a cost-effectiveness plane. To calculate the confidence intervals for the ratios, bootstrapping will be done. For all analyses, a significance of 0.05 will be applied. On the process evaluation, qualitative analyses will be performed.

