**Methods/Design:**

In a RCT, 692 participants will be randomised to either the control or the intervention group. The control group will receive usual care. For the intervention group, a lifestyle intervention has been designed based on interviews and current literature. The intervention will last 6 months and will comprise 3 face-to-face and 4 telephone contacts, consisting of individual counselling aimed at increasing daily physical activity (PA) and improving dietary behaviour, and/or smoking cessation. Counselling will take place at the Occupational Health Service (OHS), and will be done according to motivational interviewing (MI). Additional written information about healthy lifestyle will also be provided to those in the intervention group. At baseline, after 6 and after 12 months, measurements will take place. Primary outcome variables will be the lifestyle behaviours of concern, i.e. daily PA, dietary intake, and smoking status. Secondary outcome variables will be body mass index (BMI), systolic and diastolic blood pressure, total and HDL blood cholesterol, Hba1c and cardio-respiratory fitness (CRF). Sickness absenteeism and cost-effectiveness will be assessed as well. Multilevel analysis will be performed to compare all outcome measures between the intervention group and the control group.

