### Randomisation and stratification

After baseline measurements, all participants will be randomly assigned to the intervention or the control group. The study population will be pre-stratified by type of work (blue collar or white collar). Randomisation will take place at the individual level. Using Random Allocation Software (Version 1.0, May 2004, Isfahan University of Medical Sciences, Iran) a random list of letters A and B will be generated for both strata. A research assistant will assign a letter to each of the two groups.

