### Sample size calculation

The sample size is based on detecting a difference in daily PA according to the guideline for moderate intensity PA. Previous PHSs (2005) showed that 38% of construction workers with an elevated CVD risk was physically inactive according to this guideline. To show a 10% difference between the intervention and the control group after 26 weeks, i.e. 38% inactivity in the control group and 28% inactivity in the intervention group, with a power of 80% and a 95% confidence interval (α = 0.05), 692 persons will be needed (346 in each group). As we expect a loss to follow-up of 20%, 866 persons will be included at baseline. Based on an assumed initial non-response of 50%, we will invite 1,732 workers. In The Netherlands, each month approximately 3,334 workers are screened in a PHS. Based on PHS data obtained in 2006, we expect that on average approximately 667 of them (20%) will fulfil the inclusion criteria. Therefore, we expect that the recruitment period will last at least 3 months. The numbers are presented in Figure 1.

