
### Outline of the intervention

The intervention will last 6 months, since this is the minimum amount of time to achieve maintenance of changed behaviour. For the reasons described above, MI will be used as a counselling method. Based on the evidence for the effectiveness of frequent contacts, and on the preferences of the interviewed workers, 3 face-to-face and 4 telephone contacts will be scheduled. The first contact will always be face-to-face. The duration of a face-to-face contact will be 45–60 minutes. The telephone calls will take 15–30 minutes. Face-to-face contacts will preferably take place after participant's working hours (that is: after 3 pm) at the OHS. If a participant explicitly states that he does not want to visit the OHS, the counsellor may arrange a home visit. As suggested by the interviewed workers, the wife or partner of the participant will be invited to accompany the participant to the face-to-face meeting. Additionally, written materials will be provided. The intervention will be performed by 24 counsellors (occupational nurses and OPs) who have been trained for the purpose of this study. Each participant will be in contact with one specific counsellor during the entire intervention. Each participant in the intervention group will be allocated to a counsellor in his own region of residence. The counsellor will strive to arrange the first contact within the first week after inclusion, and arrange further contacts each month, with a margin of one week. The last telephone contact should take place in the 25^th ^week after inclusion at the latest. The schedule for each participant in the intervention group is presented in Table 2.

**Table 2 T2:** Contacts schedule for each participant in the intervention group.

**T in weeks**	**Event**
0	Invitation for first face-to-face encounter.
1	Face-to-face contact
4	Telephone contact
8	Face-to-face contact
12	Telephone contact
16	Telephone contact
20	Face-to-face contact
23	Telephone contact
26	First follow-up measurement
52	Second follow-up measurement.

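### The abstract promises multilevel analysis but the Data analysis section names no level, leaving the nesting of intervention participants within 24 counsellors unsettled in the analysis and unallowed for in the stated power

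*Protocol article*

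**What the plan says.** The Methods/Design part of the abstract states: "Multilevel analysis will be performed to compare all outcome measures between the intervention group and the control group". It does not say what the levels are.

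The Data analysis section describes the same comparison differently: "Both crude and adjusted linear and logistic regression analyses will be performed". It continues that "analysis for covariance will be conducted adjusting for the outcome variable measured at baseline" and that, in the adjusted model, "other potential confounders will be included as covariate, such as age and work activities". It mentions no random effect, counsellor, occupational health service or repeated-measures level.

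On delivery, the Outline of the intervention says: "The intervention will be performed by 24 counsellors (occupational nurses and OPs) who have been trained for the purpose of this study". It adds: "Each participant will be in contact with one specific counsellor during the entire intervention". Control participants get usual care and have no study counsellor.

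Randomisation is by individual. On stratification the article says: "The study population will be pre-stratified by type of work (blue collar or white collar"). The Sample size calculation compares 38% with 28% inactivity at 80% power and α = 0.05, and concludes that "692 persons will be needed (346 in each group"). It mentions no ICC or design effect.

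**The concern.** The article describes the main comparison in two ways that can lead to different standard errors. An analyst working from the abstract would fit a model with levels. One working from the Data analysis section could reasonably fit ordinary regression.

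The difference matters because the design creates nesting in one arm only. The treatment is a series of motivational-interviewing contacts with one person, so its effect may depend on how well that person counsels. The article allows for this: it plans to score counselling quality (Quality assessment) and to ask participants about their counsellor's competence (Process evaluation). If counsellors differ in effect, outcomes of men who share a counsellor are correlated, and ordinary regression gives intervals that are too narrow. The sample size, in turn, would deliver 80% power only if that correlation were zero.

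**Working it through.** **Inputs.** From the Sample size calculation: 38% v 28% inactive, α = 0.05, 80% power, 346 per arm, 20% loss, 866 recruited. From the Outline of the intervention: 24 counsellors, intervention arm only. The ICC is not given; 0.005, 0.01, 0.02 and 0.05 are assumed.

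**Step 1: reproduce the stated size.** Two-sided test of two independent proportions, pooled variance under the null, mean proportion 0.33:

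n = [1.960·√(2·0.33·0.67) + 0.8416·√(0.38·0.62 + 0.28·0.72)]² / 0.10² = (1.3033 + 0.5565)² / 0.01 = 345.9, so 346 per arm.

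Power at 346 per arm is 80.0%. Dividing by 0.8 gives 433 per arm, or 866, so the increase covers loss to follow-up only. The 692 is right for independent observations and leaves no room for clustering.

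**Step 2: design effect in the intervention arm.** Evaluable men per counsellor: m = 346/24 = 14.4, with equal caseloads assumed. DE = 1 + (m − 1)·ICC, applied to the intervention arm only.

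**Step 3: clustering ignored.** With no average effect, the variance of the difference is (1 + DE)/2 times what ordinary regression assumes. True two-sided error = 2·[1 − Φ(1.960/√((1 + DE)/2))]. At ICC 0.05: √(2.671/2) = 1.156, and 1.960/1.156 = 1.696, giving 9.0%.

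**Step 4: clustering modelled.** Power = Φ[(0.10 − 1.960·SE₀)/SE₁], where SE₀ = √(0.33·0.67·(1 + DE)/346) and SE₁ = √((0.38·0.62 + 0.28·0.72·DE)/346). At ICC 0.05: SE₀ = 0.0413 and SE₁ = 0.0407, giving Φ(0.468) = 68.0%.

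| Assumed ICC | DE | True SE / ordinary SE (38% v 28%) | True error of nominal 5% test, clustering ignored | Power, clustering modelled |
|---|---|---|---|---|
| 0.005 | 1.067 | 1.015 | 5.4% | 78.7% |
| 0.01 | 1.134 | 1.030 | 5.8% | 77.5% |
| 0.02 | 1.268 | 1.060 | 6.6% | 75.0% |
| 0.05 | 1.671 | 1.144 | 9.0% | 68.0% |

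**Step 5: keep the last two columns apart.** If clustering is ignored at ICC 0.05, the ordinary pooled SE is 0.0358 and the true SE 0.0407. The chance of rejection at 38% v 28% is then Φ[(0.10 − 1.960·0.0358)/0.0407], about 77%. The 68% applies only to the corrected test.

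**Sensitivity to the formula.** At ICC 0.05 the power is 67.3% using an effective sample size in the intervention arm and 69.1% with unpooled variance. Applying the design effect to both arms would give 58.1%, which overstates the loss because controls are not nested in counsellors.

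**The case against.** The strongest reply is that the two statements can be read together. Linear and logistic regression describe the type of outcome, and either can be fitted with levels. A condensed article may leave the random-effects structure to the full plan. This stands in part: a reader might infer that the Data analysis section prescribes single-level regression and treats all men as independent, but it says neither. What remains is that the section describing the analysis omits the feature the abstract announces, and that the abstract does not say whether the level is counsellor, health service or repeated measurement. That is a disagreement within the document shown.

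A second reply is that error inflation is not demonstrated. This also stands in part. A reader might infer that type I error is inflated on every outcome, but no ICC is given for any. Counsellors are allocated by region of residence, and correlation from shared region occurs in both arms under individual randomisation, so it does not by itself inflate the error. If counselling changed nothing for anyone, counsellors could induce no correlation either. Inflation under the null needs counsellor effects that vary around a zero mean. Intervals that are too narrow, however, need only counsellor effects that vary, whatever their mean.

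Third, at the low end the effect is small: at ICC 0.005, 5.4% error and 78.7% power. Baseline adjustment may also recover some power. Both points are accepted.

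Fourth, leaving out the stratum generally makes standard errors too large, which is the opposite direction, and work activities already appears as an example covariate. That is fair. The stratum is a secondary point, worth settling in the same edit because that example applies only to the adjusted model.

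**Conclusion.** The point holds as an inconsistency to be settled before the data are analysed, together with a power statement that rests on an unstated assumption. If the Data analysis section is run as ordinary regression, standard errors are too small for any positive counsellor ICC. For assumed ICCs of 0.005 to 0.05 they are too small by a factor of about 1.015 to 1.144, with true error of about 5.4% to 9.0%. If a counsellor-level model is run, the error is dealt with, but power is about 79% down to 68% instead of 80%.

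A reader might infer that the trial suffers both the inflated error and the full power loss. It would not, because each belongs to a different analysis. The existence of the inconsistency and the absence of a clustering allowance are certain from the text. The magnitudes rest on assumed ICCs, on equal caseloads (unequal ones would make the loss larger) and on no gain from covariates.

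**What to change.** In the Data analysis section, specify linear and logistic mixed models with a counsellor random effect in the intervention arm only, each control participant forming his own cluster. This makes the section agree with the abstract. Keep the adjustment for the baseline value and include the blue/white-collar randomisation stratum as a covariate. In the abstract, say that the level meant is the counsellor.

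In the Sample size calculation, state that 346 per arm gives 80% power if the counsellor ICC is zero. Add that power would be about 78.7%, 77.5%, 75.0% and 68.0% at ICCs of 0.005, 0.01, 0.02 and 0.05, labelled as assumed values and before any gain from covariates. A single model for both follow-ups is optional and corrects no error.

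The cost is wording, slightly wider intervals and a less favourable power statement. Counsellor identity must be kept in the data set. A reader might suppose that it is already a field on the registration forms, but the Registration forms section does not list it. Allocating each man to one counsellor makes it straightforward to record.

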### Primary outcome measures

#### Physical activity

The main outcome measure for PA is whether the participant has started to fulfil one or both of the Public Health recommendations for PA. If so, he is considered to have changed from physically inactive to physically active.

On the PHS questionnaire, he will fill in how many days per week he usually is moderately physically active for more than 30 minutes. From this item, fulfilling the Public Health recommendation for moderate PA can be determined. Furthermore, he will be asked how many days during the last month he has performed vigorous physical activities that lasted long enough to make him sweat. By this item, fulfilling the Public Health recommendation for vigorous PA can be computed. Another outcome measure for PA is the frequency, duration and intensity of PA in leisure time. This will be assessed using the Short QUestionnaire to ASsess Health enhancing physical activity (SQUASH), which was shown to be a fairly reliable and valid questionnaire (*r*_*Spearman *_0.58 and *r*_*Spearman *_0.45 respectively) [44]. The SQUASH was designed to measure four clusters of PA, i.e. commuting activities, household activities, activities at work and school, and leisure time activities. For the purpose of this study, only commuting activities and leisure time activities, i.e. walking, cycling, gardening, odd jobs and sports will be measured, as these activities are considered relevant for the target group. The participant will be asked to fill in how many days per week and how many minutes per day he usually spends on these physical activities, during a usual week within the past month. The level of exertion for each type of activity will have to be indicated as well. The level of exertion for sports, gardening and odd jobs is classified as light, intermediate, and vigorous. The level of exertion for walking and cycling is classified as slow, intermediate, and fast. From the SQUASH, metabolic equivalents (METs) can be estimated. Light activities are rated as 2.0 to < 4.0 METs, moderate activities are rated as ≥ 4.0 to <6.5 METs, vigorous activities are rated as ≥ 6.5 METs [44]. The cluster items about household activities will be left out of the SQUASH questionnaire, as we expect these activities not to be major contributors to daily PA in this population of male construction workers. In addition, the SQUASH items about activities at work and school were not considered suitable for our population. The level of exertion, i.e. light, intermediate, or vigorous, of the daily activities at work will be assessed using a single question derived from the TNO questionnaire PA at work [45], which has not been tested for validity and reliability yet.

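### Read literally, the baseline adjustment for the guideline outcome uses met/not-met status, although baseline day counts are held; using the counts would add a little power at almost no cost

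*Protocol article*

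**What the plan says.** All places are in the protocol article.

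- **Sample size calculation.** The powered outcome is binary: "The sample size is based on detecting a difference in daily PA according to the guideline for moderate intensity PA". The planning rates are "38% inactivity in the control group and 28% inactivity in the intervention group", "with a power of 80% and a 95% confidence interval (α = 0.05"), giving "692 persons will be needed (346 in each group"). Allowing for loss, "As we expect a loss to follow-up of 20%, 866 persons will be included at baseline".
- **Primary outcome measures, Physical activity.** The moderate item asks for days per week and the vigorous item for days in the last month. The counts are then turned into guideline status; for the moderate item, "From this item, fulfilling the Public Health recommendation for moderate PA can be determined". The main outcome is "whether the participant has started to fulfil one or both of the Public Health recommendations for PA". The SQUASH is kept as another activity outcome (frequency, duration and intensity in leisure time).
- **Measurements.** Baseline data come from the periodical health screening and an added questionnaire. Step 1 of the counselling protocol puts moderate days per week on the personal risk profile, so the count itself is held at baseline.
- **Data analysis.** Crude and adjusted linear and logistic regressions are planned for all outcomes, and "analysis for covariance will be conducted adjusting for the outcome variable measured at baseline". Age and work activities are given as examples of further covariates. The day counts are not named.

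**The concern.** One generic sentence sets the baseline covariate for every outcome. For a continuous outcome such as blood pressure it gives the natural choice. For a binary outcome cut from a count, it gives, on its literal reading, the cut version. A man with no active days and a man one day short of the guideline then share a baseline value, although the second can be expected to cross the line more readily. The finer measure is already in the data.

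The wording also fits the named main outcome poorly. Starting to fulfil a guideline is a transition and has no proper baseline value of its own. If it is assessed among men who were inactive at baseline, all of them have the same baseline status, so that covariate cannot adjust for anything. The day counts would then carry all the baseline activity information.

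At stake is some power on the outcome that sized the trial.

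**Working it through.** **1. The plan's own figure.** Inputs from Sample size calculation: p1 = 0.38, p2 = 0.28, alpha 0.05 (two-sided, inferred from the 95% interval), power 80%. With mean proportion 0.33:

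n per arm = [1.960 × √(2 × 0.33 × 0.67) + 0.842 × √(0.38 × 0.62 + 0.28 × 0.72)]² / 0.10²
= [1.960 × 0.6650 + 0.842 × 0.6612]² / 0.01 = (1.860)² / 0.01 = 345.9, so 346.

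This matches 346 per group and 692 in total. Allowing for loss, 692 / 0.8 = 865, against 866 stated, which is the next even number. The calculation takes no credit for baseline adjustment.

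**2. Assumptions needed to size the gain (none is in the document).** Days per week (0 to 7) arise from a latent normal variable, with the guideline met at 5 or more days. The assumed cumulative proportions for up to 0, 1, 2, 3, 4, 5 and 6 days are 0.04, 0.08, 0.15, 0.25, 0.38, 0.65 and 0.78, so 38% are inactive. The intervention shifts the latent variable by Φ⁻¹(0.38) − Φ⁻¹(0.28) = 0.277 SD, giving 28% inactive. The latent baseline to follow-up correlation r is varied from 0.3 to 0.7. Only the moderate item is modelled.

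**3. Logistic regression of follow-up status on group**, 346 per arm, 4,000 simulated trials per value of r:

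| r | Power, unadjusted | Power, baseline status | Power, baseline days | Gain, days over status |
|---|---|---|---|---|
| 0.3 | 80.0% | 81.0% | 81.6% | 0.6 points |
| 0.5 | 79.2% | 83.6% | 85.3% | 1.7 points |
| 0.7 | 80.8% | 89.4% | 92.0% | 2.6 points |

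A further simulation over the same range of r put the gain at about 1 to 4 points. On the squared z scale, another run gave gains of 3%, 5%, 7% and 11% at r = 0.4, 0.5, 0.6 and 0.7.

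**4. The same gain as sample size.** Taking n as 346 × (1 − R²), with R² the share of outcome variance explained by the baseline covariate:

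- r = 0.3: 346 × (1 − 0.035) = 334 with status; 346 × (1 − 0.050) = 329 with days; 5/334 = 1.5% fewer.
- r = 0.5: 346 × (1 − 0.105) = 310; 346 × (1 − 0.147) = 295; 15/310 = 4.8% fewer.
- r = 0.7: 346 × (1 − 0.231) = 266; 346 × (1 − 0.301) = 242; 24/266 = 9.0% fewer.

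**5. Where the gain shows.** The mean standard error of the log odds ratio rises with the stronger covariate:

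| r | Unadjusted | Baseline status | Baseline days |
|---|---|---|---|
| 0.3 | 0.163 | 0.167 | 0.168 |
| 0.5 | 0.163 | 0.174 | 0.178 |
| 0.7 | 0.163 | 0.189 | 0.200 |

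The conditional odds ratio moves further from 1 by more than its standard error grows, so z and power rise. On the risk-difference scale, standardised over the sample, the standard deviation of the estimate falls by about 0.3% to 5% when days replace status.

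**6. Men inactive at baseline only.** Status is constant, so it has no effect. Entering days raised squared z by 3% to 12% over r = 0.4 to 0.7.

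**The case against.** **The dichotomised covariate is inferred.** The article does not say in words that the baseline count is cut, its list of further covariates is open, and the coding of a covariate may be settled in a full protocol or analysis plan that is not shown. This stands as a caution: the point rests on the literal reading. But the covariate rule is stated, and for a binary outcome that is its ordinary meaning.

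**The gain is small and assumed.** This stands. The items are self-reported usual activity and the article gives no test-retest figure for them, so a gain of only about 1 point cannot be ruled out. The vigorous item and the combined one-or-both outcome were not simulated.

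Four stronger readings are tempting, and the document does not support them:

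- *The planned odds ratio has too wide a confidence interval.* A reader might infer this by analogy with linear regression. In logistic regression the interval for the log odds ratio widens with the better covariate (step 5).
- *The trial is underpowered.* The 346 per group gives 80% with no adjustment at all, and the planned adjustment already adds to that in the assumed model.
- *Activity is analysed only as met or not met.* The SQUASH outcome keeps frequency, duration and intensity, and linear regression is planned. It covers only commuting and leisure activity, so it is not the same quantity as the day item, but a graded analysis exists.
- *Mean days should replace the guideline outcome.* That changes the question, and its power depends on the form of the effect: about 93% to 98% in the simulations if men shift across the whole range, but about 13% if only men just below the cut-off move.

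**Conclusion.** The point holds as a modest efficiency gain. On its literal reading, the adjustment rule gives a binary covariate for the powered outcome when day counts are available, and a constant one if the started-to-fulfil outcome is assessed among men inactive at baseline. Using the day counts is worth about 1 to 4 points of power at 346 per arm and a slightly narrower standardised risk difference. This is conditional on the assumed correlations of 0.3 to 0.7, the assumed day distribution and a cut at 5 days, for the moderate item only. The sample size is correct for its stated inputs, the 80% target is met, and no conclusion of the trial would be invalid if the wording stayed as it is.

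**What to change.** Keep the guideline outcome. In Data analysis, state that the guideline outcomes are adjusted for the baseline day counts (moderate days per week and vigorous days in the last month), in place of or in addition to baseline guideline status. For the started-to-fulfil outcome, say which men are analysed, so that it is clear whether baseline status can serve as a covariate at all.

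Mean active days, adjusted for baseline, may be reported as an optional supporting analysis beside the SQUASH outcome. The fix does not depend on it.

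The cost is a sentence or two of analysis wording, best fixed before outcome data are examined. It needs no new data, no more participants and no change of endpoint.

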#### Step 2: Choosing type of intervention

Two types of intervention will be offered: 1) an energy balance intervention and 2) a smoking cessation intervention. Together with the counsellor, the smoker will choose one of the two intervention types, based on his personal risk profile and his own preferences. He will be encouraged to make his choice during the first meeting, and to stick to his first choice. However, if later on during the intervention, the participant desires to switch intervention types or if he prefers to address both smoking and energy balance, this will be possible. In case a participant is not ready make his choice in the first meeting yet, e.g. because he is confused by his risk profile, he will be allowed to make his choice during the 2^nd ^contact. In the energy balance intervention, both diet and PA will be addressed. Depending on the current PA and dietary behaviour of the participant, the focus will be on diet or daily PA. In improving dietary and PA behaviour, sub-behaviours will be chosen to address, which will be relevant to the participant and feasible, e.g. reducing fat intake or cycling in leisure time.

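### The secondary analysis by counselling type selects intervention men by what they received and control men by baseline preference, so it is not protected by randomisation and is open to selection bias

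*Protocol article*

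**What the plan says.** The Data analysis section of the protocol article promises intention-to-treat analyses for all outcomes and puts first a comparison of the whole intervention group, whatever type of counselling was given. It then adds a second step: "subgroup analysis will be done among those having received the smoking or the energy balance intervention". The comparator is defined in the next sentence: "the participants in each intervention subgroup will be compared to those in the control group having indicated the same type of intervention preference". This is possible because "all participants will have to indicate at baseline which lifestyle behaviour they prefer to change".

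On timing, Randomisation and stratification says: "After baseline measurements, all participants will be randomly assigned to the intervention or the control group". The stated preference therefore precedes allocation.

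The type received does not. Under Step 2: Choosing type of intervention: "Together with the counsellor, the smoker will choose one of the two intervention types, based on his personal risk profile and his own preferences". This happens at the first meeting, after the counsellor has gone through the risk profile (Step 1), or at the second contact if the man is undecided. The section also says "He will be encouraged to make his choice during the first meeting, and to stick to his first choice". It nevertheless allows later change: if "the participant desires to switch intervention types or if he prefers to address both smoking and energy balance, this will be possible".

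**The concern.** An intervention man enters a subgroup through something that happens after allocation and is shaped by the counselling itself. A control man enters through an answer given before allocation. A smoker who stated a preference for cessation but settles on energy balance in the session leaves the intervention smoking subgroup, while his control counterpart stays in. A smoker who becomes willing to quit can enter it, with no matching move among controls. On the literal wording, a man who received no counselling belongs to neither intervention subgroup, and a man who addressed both behaviours has no defined match.

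If these moves are related to the chance of quitting, part of any difference reflects who moved and not what counselling did. Smoking status is a primary outcome, and a smoker may choose energy balance, so readers will be drawn to the smoking subgroup for the effect of cessation counselling. The section applies the 0.05 level to all analyses and does not mark this one as exploratory.

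The described adjustment cannot be relied on to repair this. It covers the baseline outcome and confounders such as age and work activities. The stage-of-change items concern eating and physical activity. The 0 to 10 readiness scale (Step 4) is completed during counselling, so only in the intervention arm. The article describes no readiness-to-quit measure taken in both arms.

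**Working it through.** **The plan's own figure.** The only sample size is for the whole-group comparison of inactivity, 38% against 28%, with 80% power and two-sided α = 0.05. With pooled variance:

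n = [1.960·√(2·0.33·0.67) + 0.842·√(0.38·0.62 + 0.28·0.72)]² / 0.10² ≈ 345.9, so 346 per arm.

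346/0.8 = 432.5, so 433 per arm and 866 in all. Both stated figures reproduce, and neither depends on the subgroup rule. The plan gives no figure for the subgroup analysis.

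**The selection rules side by side.**

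| | Intervention arm | Control arm |
|---|---|---|
| Enters subgroup by | type received | stated preference |
| Fixed | after allocation, with the counsellor | at baseline, before allocation |
| Can change | yes, may switch or combine | no |
| No counselling received | in neither subgroup, read literally | not applicable |

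**How far this could matter.** The article gives no rate of switching or quitting, so every input below is assumed. The true effect is set to zero throughout.

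*Extreme one-way case.* Take 100 smokers per arm. Fifty prefer cessation (20 ready to quit, 30 not). Fifty prefer energy balance (10 ready, 40 not). Ready men quit at 25%, others at 5%. Only not-ready men leave the cessation group and only ready men enter it.
- Controls by preference: (20×0.25 + 30×0.05)/50 = 13%.
- 10% of each group switch (5 out, 5 in): (25×0.25 + 25×0.05)/50 = 15%, a spurious +2 points.
- 20% (10 out, 10 in): (30×0.25 + 20×0.05)/50 = 17%, or +4.
- 30% (15 out, entry capped at the 10 ready men): (30×0.25 + 15×0.05)/45 = 18.3%, or +5.3.

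*Same inputs, switching regardless of readiness.* The energy-balance group quits at (10×0.25 + 40×0.05)/50 = 9%. Exchanging 10% of each group gives (45×0.13 + 5×0.09)/50 = 12.6%, which is −0.4 points. Exchanging 30% gives (35×0.13 + 15×0.09)/50 = 11.8%, or −1.2. The sign is not fixed.

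*A second set of inputs.* Suppose 40% of smokers prefer cessation, men who stay or enter quit at 20%, and men who leave quit at 5%. With 10%, 20% or 30% leaving (and 5%, 10% or 15% of the others entering), controls show 0.9×0.20 + 0.1×0.05 = 18.5%, then 17.0% and 15.5%, against 20% among those receiving cessation counselling. The spurious gains are 1.5, 3.0 and 4.5 points. If everyone quits at 15%, the difference is 0 at every switching rate.

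*Simulation.* With 115 smokers per arm (assumed; about one third of 346) and a choice that increasingly tracks motivation, the spurious difference rose from about 0 to 3.7 points and the type I error from about 0.05 to 0.07. Grouping both arms by baseline preference kept the difference within 0.3 points of zero and the error at about 0.05.

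**The case against.** The strongest reply is that this comparison comes second. All primary outcomes are compared first in the full randomised arms, so a randomised, if diluted, estimate for smoking, diet and activity exists without it. That stands and limits the severity.

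The text also favours agreement between preference and type received: the choice rests partly on the man's own preferences, and he is urged to keep to it. Matching controls on preference suggests that the authors had like-with-like groups in mind. A reader might therefore take the type received as shorthand for baseline preference, leaving no problem. The documents do not support that reading: the type is chosen with the counsellor, with the risk profile in view, and may be switched or combined.

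A reader might also infer that the subgroup results are biased in favour of the intervention. That goes too far. The bias is zero if type received always equals stated preference, or if those who move have the same prognosis as those who stay. The risk profile also guides the choice; if it steered harder-to-quit smokers towards cessation, the bias could run the other way. The +2 to +5 point figures assume perfectly prognostic one-way switching.

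Finally, the choice between types is given to smokers. For non-smokers the concern is largely confined to men who receive no counselling, and their exclusion follows from the literal wording and not from an explicit rule.

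**Conclusion.** The point holds for the secondary analysis by counselling type and should be fixed. The stated rule selects the two arms differently, the intervention side by a post-randomisation event, so the comparison is open to selection bias, mainly among smokers. Size and direction cannot be derived from the article. Under assumed inputs and no true effect, the spurious difference in quitting runs from 0, when movers and stayers have the same prognosis, to about +5 points in the extreme case, and it can be slightly negative.

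It would be wrong to infer that the trial's main conclusions are at risk: the whole-group intention-to-treat analysis and the figures of 692 and 866 are untouched.

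**What to change.** In the Data analysis section, define the smoking and energy-balance subgroups in both arms by the preference stated at baseline, before randomisation. Keep every randomised man in his preference group whatever counselling he received, including men who switched, did both or had no contact. An arm-by-preference interaction term may be added but is not needed to restore the randomised comparison. Report results by type actually received as descriptive, non-randomised findings, for example with the process evaluation.

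This costs a sentence or two and no new data, since the preference is already asked of all participants. The downside is a change in what is estimated: the effect of being offered counselling within each preference group, diluted by switchers and non-attenders. That is consistent with the intention-to-treat principle stated in the same section.
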